
### Outcomes

All tests to be performed at each measurement point will be completed on three separate days. In the morning of the first day, blood samples, anthropometric, and body composition data will be collected with the participants in a fasting state. After a light and standardized breakfast, participants will complete a physical function test battery. On the second day, muscle size and architecture of the mid-thigh along with patellar tendon mechanical properties will be assessed. On the third day, the unilateral neuromuscular performance of the lower limbs will be assessed through isometric and dynamic tests. Additionally, a progressively loaded five-repetition sit-to-stand (STS) test will be conducted. Before the baseline assessments, at least two familiarization sessions will be completed to instruct participants in the proper technique of the neuromuscular tests. A detailed scheme of the assessments and outcomes that will be evaluated during this study is shown in Table 1.

**TABLE 1 T1:** Overview of the outcomes, time points of measurements, and treatments.

[figure not shown]

*KE, knee extension; BW, body weight; HL–PRT, heavy load power–oriented resistance training; LL–PRT, light load power–oriented resistance training; IL–6, Interleukin 6; TNFα, tumoral necrosis factor alpha; CRP, C-reactive protein; T:C, testosterone:cortisol ratio; GH, growth hormone; IGF–1, insulin growth factor-1; CAF, C–terminal agrin fragment; GDF–15, growth differentiation factor 15.*

### Primary Outcomes

#### Maximal Isometric Force (MIF) and Rate of Force Development (RFD) of the Knee Extensors

For isometric strength tests, participants will be seated on a custom-built isometric chair (Telju Fitness, Spain) with knee and hip angles of 90° and 120°, respectively (180° full extension). An ankle brace together with a steel cable with minimal compliance will be used to connect the lower leg to a strain gauge cell (Linear Force SmartLead, Noraxon, United States) to register knee extension force at 1,500 Hz. Then, participants will be instructed to perform several maximal voluntary isometric contractions (MVIC), extending their knee as fast and strong as possible and holding the contraction for 3 s after the cue “ready, set, go!.” Strong verbal encouragement and visual feedback will be given in each attempt to ensure maximal efforts. Five adequate trials (separated by 60 s) will be acquired. Then, the MIF will be determined as the highest force value registered, and the RFD will be calculated as the linear slope of the time-force curve between 0–50, 0–100 and 0–200, 0–400 ms and at the maximal point of the time-RFD curve (RFD_max_).

#### Force-Velocity Relationship and Maximal Dynamic Strength in the Unilateral Leg Press Exercise

The assessments will be conducted on a horizontal leg press device (Selection MD, Technogym, Italy) instrumented with a force plate (Type 9286BA, Kistler, Switzerland) and a linear position transducer (Linear encoder, Chronojump Boscosystem, Spain). A detailed description and validation of the systematic procedure that will be followed to obtain the force-velocity relationship and maximal dynamic strength in older adults has been previously published (Alcazar et al., 2017). Briefly, the participants will perform two sets of two repetitions with the starting load equivalent to 40% of their body mass being gradually increased (5–20 kg increments) until the 1-RM is reached (failure was defined as not being able to lift a load within two attempts). From the starting position (knee and hip joint angles of 90° and 70°, respectively; full extension = 180°), the repetitions will be executed as fast as possible during the concentric phase, whereas self-preferred eccentric velocity will be demanded to warrant maximal performance in the subsequent repetition. The processing of force and velocity signals has been described previously (Rodriguez-Lopez et al., 2020). Shortly, force and velocity values from the most powerful attempts of each load (i.e., highest mean power value) will be fitted in a linear model, distinguishing between first and second repetitions (i.e., concentric-only vs. eccentric-concentric performance). Then, the theoretical maximal isometric force and maximal velocity with no load will be estimated through extrapolation of the linear regression line (force- and velocity intercepts, respectively). In addition, the maximal muscle power as well as the force and velocity at which it is produced will be determined (Alcazar et al., 2017).

#### Mid-Thigh Muscle Size and Architecture

The participants will lie on an examination table in supine position and with the legs slightly flexed with the aid of a foam roller placed beneath the knee. To allow for fluid shifts to occur, this position will be held for 15 min before examination. Brightness mode ultrasound (MyLab 25, Esaote Biomedica, Genova, Italy) images will be taken with a 50 mm, 10–15 MHz linear-array probe. The scans will be acquired at 50% of the distance between the greater trochanter and the inferior border of the lateral condyle of the femur. For muscle size quantification, three transversal panoramic scans of the rectus femoris and the vastus lateralis muscles will be obtained using the extended field of view image stitching technique. For this purpose, the examiner will acquire images by moving the prove from the medial aponeurosis of the rectus femoris to the lateral border of the vastus lateralis at constant velocity. Then, three longitudinal images of the vastus lateralis will be obtained with the probe positioned at an individually determined optimal location (characterized by parallel aponeuroses and consistency of the fascicle orientation) and aligned with the fascicle plane. Abundant transmission gel will be applied to ensure acoustic coupling with minimal pressure to avoid muscle deformation. All scans will be subsequently analyzed using Fiji image analysis software (Schindelin et al., 2012). For measurements of muscle size of the rectus femoris and vastus lateralis, the muscles’ aponeuroses will be traced to quantify the cross-sectional area. The vastus lateralis muscle architecture will be analyzed through the Simple Muscle Architecture Analysis tool for Fiji (Seynnes and Cronin, 2020). Basically, this is an automated analysis process that highlights aponeuroses and fascicles to obtain the dominant fascicle orientation (i.e., pennation angle) and estimate fascicle length.

### Secondary Outcomes

#### Quadriceps and Biceps Femoris Muscle Excitation

Wireless surface electromyography (DTS EMG sensors and Desktop DTS, Noraxon United States) will be employed to acquire the excitation levels of the quadriceps femoris muscle (rectus femoris, vastus medialis, and vastus lateralis) and the long head of the biceps femoris muscle during the unilateral knee extension and leg press neuromuscular performance tests and the assessment of the patellar tendon mechanical properties (see below). The SENIAM recommendations will be followed when placing bipolar electrodes (HEX Dual Electrodes, Noraxon, United States) onto each muscle belly after proper skin preparation (Hermens et al., 2000). Raw surface electromyography signals will be captured at 1,500 Hz, amplified and filtered with a band-pass filter between 10 and 500 Hz (common mode rejection ratio >100 dB, input impedance >100 MΩ, and gain = 500) before any other signal processing. Unless otherwise stated, raw surface electromyography signals will be rectified and smoothed by calculating the root mean square with a 100 ms time window. The resultant signals amplitudes will be normalized to the muscle-specific maximum values measured during knee extension and flexion MVIC testing (EMG AMP,% MVIC). Furthermore, total cumulative muscle excitation will be calculated as the integrated area under the EMG AMP curve (%MVIC × s). Electromyographic and force signals will be synchronously processed within commercial software (MyoResearch 3.10, Noraxon, United States).

#### Patellar Tendon Mechanical Properties

The morphology of the patellar tendon at rest will be assessed with the same ultrasound system also used for measurements of muscle size and architecture. For this purpose, the participants will be accommodated (after a 5-min cycle ergometer warm-up) on the custom-built chair used for isometric strength tests, with knee and hip angles of 90° and 120°, respectively (180° full extension), and their lower leg connected to a strain gauge cell (see above). The extended field of view mode will be used to acquire images of the resting patellar tendon in the sagittal plane to determine its length as the distance between the tibial tuberosity and the patellar apex. In addition, the cross-sectional area of the patellar tendon will be measured at 25, 50, and 75% of the tendon length.

Prior to measurements of tendon mechanical properties, participants will perform several submaximal isometric ramp contractions with constant loading and visual feedback for tendon conditioning. Afterward, the participants will first execute three MVIC of the knee extensors, followed by three further maximal contractions of the knee flexors, with all contractions being separated by 60-s rest intervals. These tests will serve for the normalization of the electromyographic signals and to establish the loading rate for the ramp isometric contractions in which tendon elongation will be measured. Then, the ultrasound probe will be positioned on the patellar tendon in the sagittal plane, with both the patella and tibial tuberosity in the field of view. A demonstrative image of this experimental setting is shown in Figure 2. Ultrasound video sequences will be recorded at 24 Hz while participants perform eight appropriate ramp contractions of the knee extensors. The loading rate will be standardized, such that participants gradually increase the level of force produced from 0 to 80% of maximal isometric force over 4 s and then relax at the same controlled rate. The acquired force signals superimposed over a target template will be shown on a screen to provide instant feedback to participants (MyoResearch XP, Noraxon, United States). One minute of rest will be granted between trials.

**FIGURE 2 F2:**
[figure not shown]
Demonstrative example of the experimental setting for acquisition of *in vivo* patellar tendon behavior during isometric ramp contractions **(A)**. Field of view of ultrasound images collected from the patellar tendon **(B)**. White arrows indicate points on patella **(left)** and tibial tuberosity **(right)** that will be tracked to determine tendon elongation.

All image processing will be performed offline. First, tendon elongation will be measured as the proximodistal component of the displacement of the patellar apex relative to the tibial plateau. The points of interest will be tracked using a semi-automated software (Tracker 4.91)^1^, allowing to obtain the continuous force-tendon length data for the subsequent analysis of tendon mechanical properties. Force and electromyographic signals (1,500 Hz) will be synchronized with ultrasound video (24 Hz) data using an MS Excel^®^ spreadsheet. The further processing will be performed using custom-made MATLAB^®^ routines (MATLAB R2014b, MathWorks, Natick, MA, United States). The knee extension torque will be calculated as the product of knee extension force and the distance between the center of rotation of the knee and the position of the ankle brace just proximal to the malleoli. Then, this product will be divided by the individual patellar tendon moment arm, estimated from femoral length (Visser et al., 1990), to obtain tendon force. Tendon stress will be calculated by dividing tendon force by the average of the patellar tendon cross-sectional area as measured at 25, 50, and 75% of tendon length. Tendon strain will be computed as the change in length in relation to resting tendon length. Individual force-tendon elongation curves will be fitted with second or third order polynomials. Then, tendon stiffness (Δforce/Δelongation) and Young’s modulus (Δstress/Δstrain) will be calculated as the slope of the fitted polynomials in the final 10% of force-elongation and stress-strain curves, respectively, of the weakest valid trial.

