### Participants

The sample size was determined by an *a priori* power analysis using G^∗^Power v3 software for MS Windows^®^ (Faul et al., 2007). The effect size value used for calculations was *d* = 0.25 based on a previous study comparing peak power adaptations after a 12-week heavy- vs. light-load PRT in older adults (de Vos et al., 2005). Then, we considered three levels for the between-subject factor (i.e., one for each study arm) and three levels for the within-subject factor (i.e., three repeated measures) setting the alpha error probability at 0.05, a 1−β of 0.95 and assuming a correlation among repeated measures of *r* = 0.8. The model indicated a minimum total sample size of 24 individuals, but considering a 25% dropout rate, we have decided to enroll at least 30 participants in total. People aged 65 years and over, non-institutionalized and without serious mobility limitations will be encouraged to participate. Principally, the volunteers will be recruited among participants involved in non-exercise studies previously conducted by our research group, local advertisements posted in public places and informative talks about healthy aging. After accepting to participate, the volunteers will undergo a physical examination by a geriatrician. The criteria for exclusion are: (i) frailty status (Fried et al., 2001) or low levels of physical function (i.e., Short Physical Performance Battery <7 points) (Guralnik et al., 1994), (ii) neurological, musculoskeletal, or other disorders that might preclude subjects from completing the resistance training and all performance tests, (iii) uncontrolled hypertension, unstable or exercise-induced angina pectoris or myocardial ischemia or any other medical condition that would interfere with testing or increase subjects’ risk of complications during exercise, (iv) history of regular resistance exercise during the previous 3 years, and (v) total or partial knee replacement (i.e., prosthesis). All participants will be informed orally and in written form about the purpose, procedures, benefits, risks, and potential discomfort related to study participation before signing a consent form. This study will be conducted in accordance with the Helsinki declaration.

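### As worded, tendon stiffness and Young's modulus come from one of eight recorded ramps, so ramp-to-ramp error is not averaged out of a secondary outcome

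*Protocol article*

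**What the plan says.** Protocol article, Patellar Tendon Mechanical Properties (listed under "Secondary Outcomes"): ultrasound video is recorded "while participants perform eight appropriate ramp contractions of the knee extensors". All ramps follow one on-screen template, in which participants "gradually increase the level of force produced from 0 to 80% of maximal isometric force over 4 s". Within a session the ramps are therefore replicates of one task.

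The processing text after Figure 2 says: "Individual force-tendon elongation curves will be fitted with second or third order polynomials". Stiffness and modulus are then the slopes "in the final 10% of force-elongation and stress-strain curves, respectively, of the weakest valid trial". No averaging over ramps is stated. The same paragraph does state averaging for tendon cross-sectional area, over three sites. It does not define a valid trial or give a reason for choosing the weakest one.

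Under Statistical Analysis, outcomes are analysed as changes from week 0 to week 8 and from week 8 to week 20, with the baseline value as a covariate.

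**The concern.** If one ramp supplies the visit value, everything particular to that ramp stays in it: how the two bony points were tracked, how well the template was followed, and how the polynomial behaved at its upper end, where a fitted curve is least constrained. A change score carries this error from both visits. The ramp is chosen for low force, not for tracking quality.

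What is at stake is precision. The Discussion names muscle-tendon behaviour among the mechanisms of interest. With 30 people allocated equally to three arms, the heavy-versus-light comparison rests on about 20 heavy-load and 20 light-load legs, with 10 people contributing one of each. Avoidable measurement error widens the intervals for those contrasts, although more recordings are already planned than the stated rule uses.

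**Working it through.** **1. The plan's own figure.** The article gives no between-ramp SD, intraclass correlation or typical error for stiffness, so there is no figure on this point to reproduce. Its only computed figure is the minimum sample of 24 (Participants). For the group-by-time interaction, λ = N·m·f²/(1−ρ) = 24 × 3 × 0.25²/(1 − 0.8) = 22.5 with 4 and 42 degrees of freedom. This gives power 0.965, and 24 is the smallest multiple of three that reaches the target in "setting the alpha error probability at 0.05, a 1−β of 0.95". It reproduces if 0.25 is read as Cohen's f. It rests on peak power and takes no tendon input, so nothing below alters it.

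**2. Model (variances assumed).** Let s² be error variance shared by all ramps of a visit, t² the ramp-specific error variance, and k = t²/s². With m ramps averaged, the error variance of a change is 2(s² + t²/m). The ratio for one ramp against the mean of m is

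R = (1 + k)/(1 + k/m).

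| k | against mean of 8 | against mean of 4 | against mean of 3 |
|---|---|---|---|
| 0.1 | 1.1/1.0125 = 1.09 | 1.07 | 1.06 |
| 0.25 | 1.25/1.03125 = 1.21 | 1.18 | 1.15 |
| 0.5 | 1.5/1.0625 = 1.41 | 1.33 | 1.29 |
| 1 | 2/1.125 = 1.78 | 1.60 | 1.50 |
| 2 | 3/1.25 = 2.40 | 2.00 | 1.80 |
| 4 | 5/1.5 = 3.33 | 2.50 | 2.14 |

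The column for four applies if the eight ramps are split over two legs; the text does not say whether eight is per leg.

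**3. The same range in terms of shared error.** If a fraction h = 1/(1 + k) of single-ramp error variance is common to the session, R = 1/(h + (1 − h)/8):

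- h = 0.90: 1/0.9125 = 1.10
- h = 0.75: 1/0.78125 = 1.28
- h = 0.50: 1/0.5625 = 1.78
- h = 0.20 (k = 4): 1/0.30 = 3.33

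**4. Effect on total change variance.** True differences in response add a term that averaging cannot remove. As an illustration, let that term equal the single-ramp error variance of change. The ratio of total variances is then 2R/(R + 1):

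- R = 1.09: 1.04
- R = 1.78: 1.28
- R = 3.33: 1.54

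On the SD scale, which governs interval width, these are 1.02, 1.13 and 1.24.

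**5. Direction.** If ramps have equal error variance, the mean of several cannot have a larger error variance than one of them, whatever the correlation between their errors. The direction of the benefit does not depend on k; its size does.

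**The case against.** - **The sentence may mean something else.** The text speaks of fitting individual curves before it mentions the weakest trial. That trial may serve only to fix a force range that every ramp reaches, over which all curves are read. A reader might infer that seven recordings are discarded, but the article does not say so. It does not say that all eight are valid or belong to one leg either. This stands, and it turns part of the fix into a rewording.
- **A journal article condenses the full protocol.** This would excuse silence. Here the article states a derivation rule, and on its plain wording the rule uses one trial.
- **Much error may be common to the session.** Probe placement, the moment arm and the maximal-force reference are shared by all ramps, as are cross-sectional area and resting length for the modulus. Averaging ramps removes none of that error. This stands, and it is why the range starts near 1.1.
- **Larger losses can be produced by assumption.** At k = 9 the ratio against eight ramps is 10/2.125 = 4.7. That needs ramp variance nine times the shared variance, which nothing in the document supports.
- **Bias.** A reader might infer that choosing an extreme trial biases the comparison of loads. The weakest ramp is extreme in force. If peak force varies around the 80% target with an assumed CV of 1% to 5%, the expected minimum of eight is 78.9% down to 74.3% of maximal force. The ramp is not selected on stiffness, and the same rule applies to every leg and visit. No bias between loads is shown.

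**Conclusion.** The point holds as a precision issue in a secondary outcome. As worded, stiffness and modulus rest on one ramp although eight are recorded, and ramp-specific error stays in every change score. The cost in measurement-error variance of change, against the mean of eight, is about 1.1 times (k = 0.1, or 90% of error shared within the session) to 3.3 times (k = 4). It is less in total change variance. Both ends of this range are assumptions, because the article gives no between-ramp variance. It does not follow that recordings are certainly discarded, that either load is favoured, or that the primary outcomes or sample size are affected. The change is worthwhile because its direction is certain and it uses videos already planned.

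**What to change.** Rewrite the sentence so that the weakest valid ramp sets only the common upper force. Compute the slope over that same force window for each valid ramp of the leg at that visit, and analyse the mean over the valid ramps, with at least three. State whether eight ramps means per leg, and what makes a ramp valid. If the sentence already meant a common force window for all ramps, say so; the rewording then costs nothing.

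The cost is offline semi-automated tracking. One ramp per leg and visit is 30 × 2 × 3 = 180 videos. Three ramps make 540, three times the work. Eight ramps make 1,440, eight times the work, if eight are recorded per leg. No new visits, procedures or participants are needed.

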#### Anthropometric and Body Composition Assessments

Participants height, body mass, and body mass index will be assessed using a stadiometer and scale device (Seca 711, Seca, Hamburg, Germany). Total and appendicular body composition (i.e., absolute and relative bone, muscle and fat content) will be determined using a calibrated dual-energy X-ray absorptiometry (DXA) device (Hologic Series Discovery QDR densitometer; Hologic, Bedford, MA, United States). In addition to the whole body scans, bone mineral content and density will be determined from the lumbar spine (L1–L4) and the proximal region of both femurs (total hip, greater trochanter, intertrochanter, Ward’s triangle, and femoral neck). All DXA scans will be analyzed using Physician’s Viewer, APEX System Software Version 3.1.2 (Hologic, Bedford, MA, United States).

#### Physical Function Test Battery

A wide battery of test will be used to evaluate the physical function of participants. Firstly, the Short Physical Performance Battery will be conducted, which evaluates static balance, 4-m habitual gait speed and five-repetition sit-to-stand time (Guralnik et al., 1994). In addition, 4.5-m habitual gait speed and 30-m maximal gait speed will be also examined. The handgrip strength will be registered during a maximal isometric contraction using a digital dynamometer (Takei TKK 5401, Tokyo, Japan). For this purpose, participants will be instructed to let their arms hang straight and slightly abduct their shoulders. Finally, participants will complete a 3-m timed up and go test, which consists of getting up from a chair, walking around a cone located 3-m in front of the chair and sitting down again as fast as possible. Two appropriate trials will be collected from each test, registering the better of both performances.

#### Progressively Loaded 5-Repetition Sit-to-Stand Test

In addition to the tests included in the Short Physical Performance Battery, participants will perform an additional repeated sit-to-stand test with increasing loads. Starting from a seated position on a standardized armless chair with their feet over a force-plate and their arms crossed over the chest, they will be encouraged to complete five repetitions (rising to a full standing position and return to the original sitting position) as rapidly as possible. The test will be conducted under unloaded and loaded conditions: 0%, 10%, and 20% of the participant’s body mass. The better of two adequate trials in each loading condition will be registered. One minute of passive recovery will be guaranteed between trials. A video camera (HD Pro Webcam C920 1080p, 30 Hz, Logitech, Switzerland) will record all trials from the sagittal plane. Concentric and eccentric phases of the movement will be detected offline examining force and video signals synchronized within a specialized software (MyoResearch 3.10, Noraxon, United States). Mean force will be collected with the force plate. STS vertical displacement will be calculated as leg length (from the superior border of the greater trochanter of the femur to the inferior border of the calcaneus bone) minus the height of the chair from the top of the force plate (0.43 m). Then, mean velocity of each STS repetition will be calculated as the ratio between STS vertical distance and time elapsed during the concentric phase. Finally, mean power during each repetition will be determined as the product of mean force and mean velocity values.

